## Abstract

**Background:**

Communication is a critical component of the patient-provider relationship; however, limited research exists on the role of nonverbal communication. Virtual human training is an informatics-based educational strategy that offers various benefits in communication skill training directed at providers. Recent informatics-based interventions aimed at improving communication have mainly focused on verbal communication, yet research is needed to better understand how virtual humans can improve verbal and nonverbal communication and further elucidate the patient-provider dyad.

**Objective:**

The purpose of this study is to enhance a conceptual model that incorporates technology to examine verbal and nonverbal components of communication and develop a nonverbal assessment that will be included in the virtual simulation for further testing.

**Methods:**

This study will consist of a multistage mixed methods design, including convergent and exploratory sequential components. A convergent mixed methods study will be conducted to examine the mediating effects of nonverbal communication. Quantitative (eg, MPathic game scores, Kinect nonverbal data, objective structured clinical examination communication score, and Roter Interaction Analysis System and Facial Action Coding System coding of video) and qualitative data (eg, video recordings of MPathic–virtual reality [VR] interventions and student reflections) will be collected simultaneously. Data will be merged to determine the most crucial components of nonverbal behavior in human-computer interaction. An exploratory sequential design will proceed, consisting of a grounded theory qualitative phase. Using theoretical, purposeful sampling, interviews will be conducted with oncology providers probing intentional nonverbal behaviors. The qualitative findings will aid the development of a nonverbal communication model that will be included in a virtual human. The subsequent quantitative strand will incorporate and validate a new automated nonverbal communication behavior assessment into the virtual human simulation, MPathic-VR, by assessing interrater reliability, code interactions, and dyadic data analysis by comparing Kinect responses (system recorded) to manually scored records for specific nonverbal behaviors. Data will be integrated using building integration to develop the automated nonverbal communication behavior assessment and conduct a quality check of these nonverbal features.

**Results:**

Secondary data from the MPathic-VR randomized controlled trial data set (210 medical students and 840 video recordings of interactions) were analyzed in the first part of this study. Results showed differential experiences by performance in the intervention group. Following the analysis of the convergent design, participants consisting of medical providers (n=30) will be recruited for the qualitative phase of the subsequent exploratory sequential design. We plan to complete data collection by July 2023 to analyze and integrate these findings.

**Conclusions:**

The results from this study contribute to the improvement of patient-provider communication, both verbal and nonverbal, including the dissemination of health information and health outcomes for patients. Further, this research aims to transfer to various topical areas, including medication safety, informed consent processes, patient instructions, and treatment adherence between patients and providers.

**International Registered Report Identifier (IRRID):**

DERR1-10.2196/46601

## Introduction

### Overview

The most important component of the patient-provider encounter is communication [1,2]. This finding has been reinforced by the National Cancer Institute model of patient-centered communication [3]. A recent meta-analysis of randomized controlled trials found a statistically significant effect (Cohen *d*=0.11; *P*=.02) on patient outcomes [4], consistent with other systematic reviews [5,6]. Poor patient-provider communication represents a pressing public health issue associated with increased medical errors and malpractice [1,7-11]. Communication has been shown to be a driver of patient satisfaction and outcomes and is closely connected with patient-centered care [9,10,12]. Collectively, these reports stress the public health importance of health communication and the need for interventions to improve providers’ health communication.

Research on verbal health communication has led to important insights into information dissemination in the patient-provider encounter. However, less is known about nonverbal communication despite its equal importance [4]. Mehrabian and Ferris [13] reported that only 7% of emotional communication is conveyed verbally, 38% is conveyed by voice tone and inflections, and 55% is transferred by facial expressions [1,14,15]. Health issues, such as cancer, evoke fear, anxiety, and uncertainty. Patients are keen on subtle cues communicated both verbally and nonverbally [16]. For example, increased direct clinician body orientation is associated with increased patient satisfaction and understanding [17]. Inconsistency between verbal and nonverbal communication is detrimental to patient-centeredness because patients likely perceive these inconsistencies as disingenuous [1]. Henry et al’s [18] systematic review of nonverbal communication found an association between nonverbal communication (global affect, warmth, negativity, listening, etc) and patient satisfaction. Connection to patient outcomes was less clear but also less researched, potentially due to the lack of a systematic assessment of nonverbal behavior. The authors called for developing consistent and validated measures of nonverbal communication and urged that “studies of facial expression might analyze patients’ and clinicians’ expressions at the dyadic rather than the individual level” with dyadic data analysis [18]. Thus, better assessment of nonverbal communication and application of appropriate dyadic statistics are needed.

Communication interventions directed at providers tend to provide communication skills training in a variety of formats, such as courses, workshops, or training videos [6]. One promising informatics-based educational strategy is virtual human training. Technology-based avatars and virtual humans have been developed to address cognitive tasks [19], such as verbal communication [20,21] and reasoning for diagnosis and therapy [22]. However, this body of literature is relatively nascent, particularly related to health communication. Research on virtual humans to enhance health communication has the potential to train medical students and nurses [23,24], as virtual humans offer a unique advantage by providing an authentic, safe simulated environment to learn with the appropriate level of challenge [25]. Users perceive virtual human interactions as real [26], and learners feel a social presence that can enhance learning and engagement [25,27,28]. After receiving feedback, the professional can immediately practice and implement the feedback, which is crucial to developing communication skills [29]. In contrast to human-standardized patients, virtual humans offer needed training without becoming fatigued. As a result, interactive and engaged virtual human informatics–based interventions demonstrate promise in enhancing communication.

Improving communication skills requires a reliable and valid method to assess them. Many communication assessments focus on verbal communication. These methods involve coding recorded interactions, such as the evidence-based Roter Interaction Analysis System (RIAS) [30], which has 41 categories, including a global affect rating (eg, voice tone) and the use of standardized patients instructors (SPIs) in simulated interactions [31] to evaluate performance. A nonverbal assessment is the Facial Action Coding System (FACS), which delineates observable components of facial movement into action units [32,33]. However, these are typically used for summative assessment of interventions or competence. Virtual human and informatics simulations have the potential to use assessment formatively by assessing behavior, providing automated feedback to the user, and giving further opportunities to practice. Educators often distinguish “assessment for learning” (ie, formative) with “assessment of learning” (ie, summative) because strategic use of formative assessment provides a more tailored, engaging experience with better outcomes [34,35]. Unfortunately, with few exceptions [23,36,37], interventions tend to rely on verbal assessment and standardized patients as a summative assessment only, rather than feeding results into the intervention as a formative assessment.

Standardized patients are widely used but are also costly, fatigue-prone, and have reliability concerns. SPIs have been used in objective structured clinical examinations (OSCEs) to assess verbal and nonverbal communication and provide feedback to learners. SPIs and OSCEs are a gold standard in communication assessment and are used in many interventions, including the MPathic–virtual reality [VR] trial, to assess primary outcomes. Yet, the cost of developing the scenarios, finding and hiring SPIs to conduct 1 OSCE, training to reach interrater reliability, and ongoing maintenance training is high. Published costs were estimated at US $35 per student in the United States in 1994 [38] and more recently in 2011 at US $90 per student in a European study [39]. The personnel time required for 1 OSCE has been reported as 104 hours for supervision, monitoring, logistics, and evaluation [39]. Finally, SPIs are prone to fatigue and excessive mental workload, which limits their ability to correctly identify and report on critical conversational and behavioral cues [40]. Therefore, SPIs are costly and best suited for summative assessment.

These informatics-based interventions to improve communication have primarily focused on verbal aspects. A recent innovation is an automated nonverbal feedback and detection system based on teleconferencing with an SPI, as reported by researchers in an Australian medical school [37]. The researchers demonstrated the utility of automated feedback on nonverbal behavior. In a randomized crossover trial, they found the system useful for enhancing medical communication and a statistically significant improvement over the standard curriculum component based on assessments by an SPI. Mpathic-VR, a virtual human simulation, has also assessed nonverbal communication by providing instructions to the user and by collecting sensor data (unanalyzed to date and a focus of this study) on nonverbal behaviors demonstrated. It also included an assessment of nonverbal behavior as 1 of 4 domains in a follow-up OSCE about 1 week post intervention, which indicates training transfer. It is important to note that communication may vary across in-person and telehealth visits. For example, clinicians tend to display more dominant behaviors, fewer empathy utterances, and portray an increased sense of urgency in telehealth visits [41].

One area that remains unclear is how nonverbal behavior is a mediating factor in communication competence, the accuracy of this nonverbal assessment, and whether the assessment is patient-centered. As a mediating factor, a potential path is that the system provides instruction on nonverbal communication (ie, stimulus), which prompts the learners to follow those instructions, leading to improved nonverbal communication as assessed by the Mpathic-VR and the follow-up OSCE. A path model is needed to test these assumptions, beginning with the extent to which the learner followed instructions. Although the data exist in this data set to test that path model, it has not yet been investigated. Understanding the mediating influence of nonverbal communication is essential to fully integrate nonverbal aspects into virtual human technology.

### Conceptual Frameworks

This study is guided by several conceptual frameworks, including frameworks for analysis of human factors and virtual human intervention.

#### Conceptual Framework for Analysis of Human Factors

Two models help guide the analysis of the human-computer interaction with the virtual human and the understanding of the mediation of nonverbal behavior. Stanney et al’s [42] human factors in virtual environments (Figure 1) provide a model for systematic informatics research to harness the potential of virtual environments [42]. Second, the Activity Theory–based Model of Serious Games posits 3 interrelated activities contribute—instructional (what MPathic intrinsically teaches), learning (communication outcomes), and gaming (interacting with MPathic) [43]. This model is a framework for analyzing the relationship between the virtual human and educational goals. Teaching communication principles is not enough, and MPathic incorporates audit and feedback principles to reinforce lessons and promote sustained change [44]. A major outcome of this study is to better understand computer-human interaction to ensure a realistic experience that drives behavior change.

**Figure 1 figure1:**
[figure not shown]
Human factors in virtual human environment. Adapted from Stanney et al [42].

#### Conceptual Framework for the Virtual Human Intervention

Previous work has developed broad models of patient-centered communication (Figure 2) that guide the virtual human’s instructional tasks. The National Cancer Institute’s model of Patient-Centered Communication in Cancer Care [3] posits that patient-centered care and clinicians skilled in communication lead to improved health communication, which leads to improved health outcomes. Effective communication requires that patients and clinicians have “knowledge, understanding, and self-awareness of what is required to communicate effectively” and the skills to do so. In the Patient-Centered Communication model and consistent with educational theory [45], motivation of all parties is necessary to enhance communication skills. Additionally, health outcomes improve with attention to 6 core communication functions: (1) responding to emotions, (2) exchanging information, (3) making decisions, (4) fostering healing relationships, (5) enabling patient self-management, and (6) managing uncertainty. Nonverbal behavior can be mapped onto these core functions. An intervention that targets these core functions—both verbal and nonverbal aspects—to develop skills and attend to motivation through an engaging learning experience may overcome the limitations of these training models.

**Figure 2 figure2:**
[figure not shown]
Conceptual model of core functions of patient-clinician communication. Adapted from Epstein and Street [3].

### Study Aims

This research aims to improve providers’ dissemination of health information and related health outcomes for patients through an enhanced conceptual model of patient-centered communication that not only describes core communication functions but also presents a directional model of the interrelationships between those components. That conceptual model will be critical to incorporate into the technology to address verbal and nonverbal communication more comprehensively. Finally, this research will build the nonverbal assessment and automated feedback directly into the virtual human simulation for testing. This research has implications for a wide range of disease areas and broad applicability to medication safety, informed consent processes, patient instructions, and treatment adherence.

## Methods

### Overview

This research will use a multistage mixed methods design that includes convergent and exploratory sequential components (Table 1). The first phase will use a convergent design that merges [47] qualitative and quantitative MPathic-VR data to better understand the mediating influence of nonverbal communication (aim 1). Next, an exploratory sequential design will follow that begins with a qualitative grounded theory exploration through patient interviews. This information will be used to build [47] an automated nonverbal communication behavior assessment (aim 2). These findings will be used to develop the virtual human software’s nonverbal assessment and conduct a quality control check as a small pilot of the enhanced system (aim 3).

**Table 1 table1:** Summary of research design: data sources, analysis, and outcomes of each phase.

Aim	Data collection procedures	Data analysis procedures	Product or outcome
(1) Mediating effects nonverbal communication	Quantitative: MPathic game scores, Kinect nonverbal data, OSCE^a^ communication score, RIAS^b^ and FACS^c^ coding of video Qualitative: video recording of MPathic-VR interactions, student reflections	Dyadic data analysis, path modeling Thematic analysis of video data, followed by data transformation to quantify it	Understand what elements of the nonverbal behavior construct are most important in the human-computer interaction
(2) Develop model of nonverbal communication	Interviews with oncology providers about intentional nonverbal behaviors (eg, mirroring, silence, and nodding)	Grounded theory qualitative analysis: open coding and relating components to develop the model	Model of nonverbal communication; function to include in virtual human
(3) Add and validate a new automated nonverbal communication behavior assessment in MPathic-VR	Qualitative findings inform development of assessment along with FACS and RIAS models; Providers use MPathic-VR and assess if the system detects nonverbal behavior	Mixed methods to build assessment: codes → variables, quotes → item language, interrater reliability analysis; code interactions, dyadic data analysis	Updated virtual human with new automated nonverbal communication behavior assessment; initial quality control data

^a^OSCE: objective structured clinical examination.

^b^RIAS: Roter Interaction Analysis System.

^c^FACS: Facial Action Coding System.

### Convergent Mixed Methods Design

#### Overview

A mixed methods convergent design [48] will be used that integrates qualitative nonverbal assessment and student reflections with quantitative MPathic-VR game data and OSCE communication skill scores. The results generated from the convergent mixed methods design will help identify the mediating influence of nonverbal behavior and what nonverbal elements of the intervention were most important.

#### Data Collection

Data will be collected from the MPathic-VR to investigate the mediating influence of nonverbal behavior in virtual human intervention. Although results from the trial indicated a positive effect, it is imperative to understand what aspects of nonverbal communication were most predictive of outcomes. To address this, a large amount of data will be gathered from 210 participants in the MPathic-VR intervention arm (that has not yet been previously analyzed) to understand the extent and mechanism by which nonverbal communication influenced outcomes. Data include video recording MP4 files for each of 4 interactions (840 videos), MPathic-VR scores (continuous data) that reflect the path through the system and responses for each participant, a warehouse of nonverbal sensor data (binary data) recorded by the Microsoft Kinect sensor for 4 nonverbal behaviors (eg, nodding, shaking head, smiles, and proximity), OSCE performance scores (5-point rating for 4 domains and a continuous global score), and qualitative written reflections from the medical students.

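### Aim 1 promises the mediating effect of nonverbal communication but uses only intervention-arm learners, so it can support within-arm associations with OSCE score, not mediation of the intervention's effect

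*Protocol article*

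**What the plan says.** The Abstract (Methods) states the purpose of the first phase: "A convergent mixed methods study will be conducted to examine the mediating effects of nonverbal communication". Table 1 gives Aim 1 the same label. The Overview of the Convergent Mixed Methods Design says that its results "will help identify the mediating influence of nonverbal behavior", and the Data Collection section below it adds that the aim is to learn how far and by what mechanism nonverbal communication affected outcomes.

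The Introduction (Overview) sets out the path: "a potential path is that the system provides instruction on nonverbal communication (ie, stimulus), which prompts the learners to follow those instructions". Better nonverbal communication, in MPathic-VR and at the follow-up OSCE, is the end of that path. The same paragraph says that the existing data are enough to test the path model.

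The data are fixed in Data Collection: "a large amount of data will be gathered from 210 participants in the MPathic-VR intervention arm". They comprise videos, game scores, Kinect sensor data, OSCE scores and written reflections. Data Analysis and Integration plans a structural equation model and an R-squared for nonverbal relative to verbal behavior on the OSCE outcome. The Limitations section covers coder drift and culture.

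**The concern.** A mediating effect of an intervention has two links: the intervention changes the mediator, and the mediator changes the outcome. Estimating the first link needs people with and without the intervention. Aim 1 has only people with it. The second link can be fitted within one arm, but how a learner behaves is decided by the learner and not by randomisation. Someone who already communicates well may both show more of the taught behaviors and score better at the OSCE.

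At stake is what the study may conclude. A within-arm result could be reported as the mechanism of MPathic-VR when it only shows which behaviors go with higher scores. The Aim 1 results are also meant to help choose the nonverbal variables for the virtual human.

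**Working it through.** **Inputs from the article.** 210 participants, intervention arm only (Data Collection). Four interactions per participant, described as "video recording MP4 files for each of 4 interactions (840 videos" (same section). The path begins where "the system provides instruction on nonverbal communication (ie, stimulus), which prompts the learners to follow those instructions" (Introduction, Overview).

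**Step 1: reproduce the plan's count.** 210 × 4 = 840, which matches the stated number of videos. So all 210 are users of MPathic-VR. The Abstract (Results) gives the same totals: "Secondary data from the MPathic-VR randomized controlled trial data set (210 medical students and 840 video recordings of interactions". That sentence names the randomised trial as the source, but nothing in the Aim 1 text adds control-arm learners.

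**Step 2: what one arm can estimate.** Let X be the intervention (the system and its instruction), M nonverbal behavior and Y the OSCE score:

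- M = i₁ + aX + error
- Y = i₂ + c′X + bM + error
- indirect effect = a × b; total effect = c′ + a × b

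With X = 1 for everyone, the variance of X is 0 and the design matrix [1, X] has rank 1 instead of 2. Only the sums i₁ + a and i₂ + c′ can be estimated. Hence a, c′, a × b and the total effect are not estimable. The slope of Y on M within the arm is.

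**Step 3: how far the within-arm slope can mislead.** The article gives no figure for prior skill, so assume that it correlates r with both M and Y and that M has no effect on Y. The spurious correlation is then r × r, and its square is the spurious R-squared:

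| Assumed r | Spurious correlation | R-squared |
|---|---|---|
| 0.3 | 0.09 | 0.8% |
| 0.4 | 0.16 | 2.6% |
| 0.5 | 0.25 | 6.3% |

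A simulation (n = 210, 3000 runs per setting, true effect of M on Y set to 0) gave mean slopes of 0.00, 0.09 and 0.25 for r of 0, 0.3 and 0.5. The results were essentially the same whether the true effect of the intervention on behavior was set to 0 or to 0.5. Within-arm data cannot tell those two cases apart.

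**Step 4: what a second arm would add.** With an assumed 210 learners per arm and a mediator measured in both, true values of a of 0 and 0.5 were recovered as −0.001 and 0.497, each with a standard error of about 0.10. This makes a estimable. It does not remove confounding of b.

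**The case against.** The best defence is that the path model does not start from the trial arm. The Introduction describes it as "beginning with the extent to which the learner followed instructions", which varies between learners. Mirroring and use of feedback at the second attempt vary too. This stands, as far as it goes: within-arm indirect paths can be defined and fitted. A reader might infer that no indirect path of any kind exists in these data; the article does not support that. But following the nonverbal instructions is largely the proposed mediator itself, so it cannot stand in for a separate exposure.

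Second, part of the stated goal is already associational: finding the best predictors of outcome, and an R-squared. This also stands, and it makes the rewording easy. It does not cancel the mediation and mechanism wording elsewhere.

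Third, a reader might infer that the within-arm result can only be confounded. That goes too far. An article may leave the covariates of the structural equation model to a fuller plan, and adjustment could reduce confounding. No covariate list, however, can create variation in the exposure.

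Fourth, it is tempting to turn Step 3 into false-positive rates. With Fisher's z, atanh(0.09), atanh(0.16) and atanh(0.25) times √207 are 1.30, 2.32 and 3.67, so a two-sided 5% test would reject in about 25%, 64% and 96% of studies. The arithmetic is right, but Aim 1 states no significance test and the correlations are assumed. R-squared, the plan's own measure, is the fairer scale.

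Finally, a reader might infer that confounded associations alone would decide what is built into the virtual human. The article also draws on provider interviews, behavior coding, FACS and RIAS, and then runs a quality check.

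**Conclusion.** The point holds for the mediation claim. As written, Aim 1 promises an effect that its data cannot deliver: how much of the effect of MPathic-VR runs through nonverbal behavior is not estimable from the intervention arm alone. This rests on the article's own restriction to that arm and on the reading that everyone in it was exposed to the instructing system. It needs no assumed figure.

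Within-arm paths to OSCE score remain available and useful, but they are not randomised and are open to confounding. The size of that bias is unknown. The spurious correlation of 0.09 to 0.25 (R-squared about 0.8% to 6%) illustrates it under assumed correlations of 0.3 to 0.5, no true effect and no adjustment.

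**What to change.** 1. Restate the Aim 1 estimand and conclusions as the within-arm association of nonverbal behavior with OSCE score. Drop mediating effect and mechanism as conclusions about the intervention, in the Abstract, Introduction, Table 1 and Convergent Mixed Methods Design sections.
2. Add the missing comparator and confounding by prior communication skill to the Limitations.
3. Where data are held per attempt, relate second-attempt behavior to OSCE score conditional on first-attempt behavior and score. The article does not say outright that scores are held per attempt. First-attempt measures arise during the intervention, so they control for prior skill only in part. Add a sensitivity analysis for unmeasured confounding.
4. Reserve mediation claims for an analysis with a mediator and OSCE score measured in both trial arms. Control-arm OSCE scores alone would supply no Kinect or video mediator. The OSCE nonverbal domain might serve as a nonverbal measure common to both arms if control students were scored on it, which the article does not state. Mediator-outcome confounding would still need handling.

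Items 1 to 3 need no new data. The cost is a weaker claim and a little more analysis.
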